### 9.2.2. Analysis of Secondary Endpoints

The proportion of subjects with LBW is a key secondary endpoint. It is defined as the following: live-borne neonate (singleton) low birth-weight (or LBW for short, defined as live birth weight <2,500g). A secondary analysis will also be repeated using the per protocol analysis set.

All secondary efficacy endpoints that are dichotomous, expressed as a proportion, will be summarized and analyzed using the same methods as for the primary endpoint. Secondary efficacy endpoints that are not dichotomous will be analyzed using analysis of covariance (ANCOVA) when a baseline value is available, and analysis of variance (ANOVA) otherwise. The ANCOVA model will contain baseline as a covariate, as well as factors for treatment group and randomization strata. The ANOVA model will contain factors for treatment group and randomization strata.

For subjects with nasopharyngeal swabs positive for macrolide resistant and penicillin resistant *Strep. pneumoniae* (to be performed in about 600 subjects in each AZCQ arm and SP arm from at least 2 sites), the proportion positive at Baseline, Day 28-42 post delivery, and at 6 months post last AZCQ IPTp course will be computed. A listing of these subjects will also be provided.

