#### Other Secondary Efficacy Endpoints

1. Hemoglobin concentrations at 36-38 weeks of gestation;
2. Occurrence at birth of a neonate with congenital abnormalities;
3. Occurrence of a perinatal or neonatal deaths;
4. Birth weight of the live-borne neonate (singleton);
5. Number of episodes of symptomatic malaria per subject anytime from first IPTp dose administration to delivery;
6. Occurrence of a subject requiring additional treatment for malaria during the study period following the first dose (diagnosed based on clinical presentation and/or lab test results);
7. Occurrence of peripheral parasitemia at 36-38 weeks of gestation;
8. Occurrence of peripheral parasitemia at delivery;
9. Occurrence of cord blood parasitemia at delivery;
10. Occurrence of STIs including *T. pallidum*, *N. gonorrhoeae*, *C. trachomatis* during the study period following first dose (diagnosed based on clinical presentation prior to Week 36-38 and/or lab test results between Week 36-38);
11. Occurrence of a positive result for *C. trachomatis* infection at 36-38 weeks of gestation (diagnosed based on lab result);
12. Occurrence of a positive result for *N. gonorrhoeae* infection at 36-38 weeks of gestation (diagnosed based on lab result);
13. Occurrence of a positive result for *T. pallidum* test at 36-38 weeks of gestation (diagnosed based on lab result);
14. Occurrence of a *T. vaginalis* infection at 36-38 weeks of gestation (diagnosed based on lab result);

15. Occurrence of bacterial vaginosis at 36-38 weeks of gestation (diagnosed based on lab result);
16. Occurrence of ophthalmia neonatorum (diagnosed based on lab test results) in the neonate;
17. Occurrence of bacterial infections including pneumonia and other lower respiratory tract infections anytime from first IPTp dose administration to delivery;
18. Occurrence of pre-eclampsia from Week 20 to delivery;
19. Occurrence of nasopharyngeal swabs positive for macrolide resistant and penicillin resistant *Streptococcus pneumoniae* at baseline, at Day 28 (window Day 28 - Day 42) post delivery, and at about 6 months following last IPTp course. This test will be done in about 600 subjects each from the AZCQ and SP arms from two or more sites.

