#### 4.1. Inclusion Criteria

Subject eligibility should be reviewed and documented by an appropriately qualified member of the investigator's study team before that subject is included in the study. Subjects must meet all of the following inclusion criteria on Day 0 at Visit 1 to be eligible for enrollment into the study:

1. Pregnant women (all gravidae) with  $\geq 14$  and  $\leq 26$  weeks of gestational age (defined by ultrasound).
2. Evidence of a personally signed and dated informed consent document indicating that the subject (or a legally acceptable representative if a subject is  $< 18$  years of age) has been informed of all pertinent aspects of the study and that all questions by the subject have been sufficiently answered. Assent will be obtained from subjects  $< 18$  years of age.
3. Subjects who are willing and able to comply with scheduled visits, treatment plan, laboratory tests, and other study procedures.

4. Subjects who agree to be supervised for treatment administration, and are available for all follow up visits as per protocol, including follow ups at delivery and on 28 days post delivery.

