#### **4.3. Randomization Criteria**

A computer-generated randomization list will be provided by the sponsor to the investigators. Randomization will be stratified according to gravidae (primigravidae & secundigravidae vs. other gravidae). Among all gravida, approximately 50% subjects will be stratified with primigravidae & secundigravidae. The investigator will assign subject identification numbers sequentially as they are determined to be eligible for treatment (PID numbers). This unique PID number will be retained throughout the study and must appear on all case report form (CRF) pages, source documents and lab data. The eligible subjects who have met all inclusion/exclusion criteria will receive study medication assigned to the next available randomization number at the Day 0 during the first study visit. The randomization number will also be recorded on the proper CRF page.

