### 7.1. Safety Assessments:

Safety and tolerability will be assessed by spontaneously reported adverse events, vital signs, physical examination, safety laboratory tests including hemoglobin and urine test for glucose and protein, and adverse pregnancy outcomes for mothers and by the general physical examination for the neonates through Day 28 (window: Day 28 to Day 42) post delivery.

- Adverse events assessments: refer to Section 8 (Adverse Event Reporting);

- Complete physical exam (including general appearance, throat, neck, thyroid, musculoskeletal, skin, lymph nodes, extremities, pulses, pulmonary, cardiac, abdominal, and neurological examination) at baseline or limited physical exam (including general appearance, brief pulmonary, cardiac, abdominal and neurological examination or symptom directed exams) at Visit 5, 6, and 7 from the activity schedule;
- Vital signs: include weight, sitting blood pressure, pulse rate and oral temperature;
- Routine obstetric checkup: include fetal height, fetal heart beat, fetal position;
- Obstetrical ultrasound: will be performed on Day 0 of Visit 1 only if urine pregnancy test is positive. The assessments include current gestational age (weeks), congenital abnormality, or any malformation.
- Laboratory tests:
  - Urine pregnancy test: will be performed if not done at any prior ANC visit for this pregnancy;
  - Hemoglobin levels: with HemoCue™, via finger stick or peripheral blood collection;
  - Urine analysis for glucose & proteins.
- Pregnancy outcomes: refer to Section 7.2 for details;
- General physical examination of the neonate at birth (within 2 days for home delivery) and at Day 28 (Day 28 - Day 42): weight, length, head circumference, APGAR scores (1/5 minutes at birth only), Ballard scores, congenital anomalies, clinical/hospital visits/stays, and other complications, etc;
- Concomitant treatment assessments.

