#### 9.5. Interim Analysis

The study will employ a group sequential design with three unblinded analyses conducted at 50%, 70% and 100% of information time (percentage of subjects with data for the primary endpoint). Group sequential stopping rules will be used to stop the trial early for efficacy and futility (futility is non binding) at each of the 2 sequential analyses.

The overall alpha level will be 1-sided 0.000625 and the power will be approximately 90% (See Section 9.1) for establishing superiority of AZCQ over SP in proportion of subjects with sub-optimal pregnancy outcome (primary endpoint). Secondary efficacy endpoints will use an overall alpha level of 1-sided 0.025. The study was designed using the EAST software Version 5.1.

To protect the Type I error rate, the gamma (-4) function will be used for alpha spending for all efficacy endpoints. Similarly, the gamma (-6) function will be used for beta spending for the primary endpoint only. Early stopping for efficacy will only occur if both the proportion of subjects with sub-optimal pregnancy outcome (primary endpoint) and the proportion of subjects with LBW (key secondary) is statistically significantly lower in the AZCQ group compared to SP, as evaluated by the relative risk (primary analysis). Early stopping for futility will only be based on the primary endpoint.

The EAST software will be used to monitor the sequential analyses. It is important to note that the critical values for the stopping boundaries will depend on the percentage of subjects actually in each sequential analysis (the actual observed percentage of information). The new critical values will be calculated within EAST subject to the pre-defined alpha and beta spending functions specified for the design, in order to maintain the appropriate overall power and significance level.

090177e1811dafca\Approved\Approved On: 22-Feb-2010 14:41

The sequential analyses will use unblinded treatment codes, and be prepared by a group within Pfizer but external to the study team. An Independent Data Monitoring Committee (IDMC) external to Pfizer will then be used to formally make decisions on stopping or continuing the study based on the interim results, the predefined stopping regions, and the interim monitoring output from EAST. The membership of the IDMC and its charter, as well as the procedures for performing the interim analyses will be finalized and documented prior to the first interim analysis.

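### Section 9.2.2 limits the birth-weight model to treatment and gravidity, leaving out maternal weight and gestational age already recorded at Visit 1: a valid analysis with a small, free precision gain unused

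*Protocol*

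**What the plan says.** Section 2.2 lists the weight of the live-born singleton as item 4 of 19 other secondary efficacy endpoints. It is neither primary nor key secondary.

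Section 9.2.2 sets one rule for all secondary endpoints that are not dichotomous: "analysis of covariance (ANCOVA) when a baseline value is available, and analysis of variance (ANOVA) otherwise". The ANCOVA carries the baseline value, treatment and strata. For the other case, "The ANOVA model will contain factors for treatment group and randomization strata". Section 4.3 names a single stratification factor, gravidity, in two levels (first or second pregnancy against later ones).

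On what is collected, Section 7.1 says "Vital signs: include weight, sitting blood pressure, pulse rate and oral temperature", and Section 6.1.1 places vital signs among the Visit 1 procedures done before therapy starts. The same visit includes the obstetric ultrasound, of which Section 7.1 says "The assessments include current gestational age (weeks), congenital abnormality, or any malformation". Section 4.1 makes an ultrasound gestational age of 14 to 26 weeks an entry condition, so it is known for every eligible woman.

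On error rates, Section 9.5 states: "Secondary efficacy endpoints will use an overall alpha level of 1-sided 0.025". No section gives a standard deviation, effect size or power for birth weight.

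**The concern.** The rule in Section 9.2.2 treats a useful covariate and a baseline value of the same variable as one thing. For hemoglobin at 36-38 weeks they coincide, because hemoglobin is measured at Visit 1, and that endpoint gets an ANCOVA. Birth weight has no earlier value of itself, so the rule leaves it with gravidity alone, although other pre-treatment measurements that may predict it are already on the case report form.

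Maternal weight is the natural candidate. Because women enter anywhere across a 12-week span of pregnancy, a recorded weight means different things at 14 and at 26 weeks. Gestational age at the same visit puts the weights on a common footing, which justifies including it even if it predicts little alone.

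What is at stake is the width of the confidence interval for the treatment difference in mean birth weight. In a linear model under randomization, leaving out a prognostic baseline covariate costs precision. It does not cause bias.

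**Working it through.** **Does the ANOVA apply to birth weight?** The endpoint is continuous (Section 2.2). It has no baseline value. Section 9.2.2 therefore sends it to the ANOVA, whose terms are listed as treatment and strata. The additional models in Section 9.2.1 (strata, HIV status, age, country) examine interactions with treatment on the primary endpoint only.

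**Are the covariates available and pre-treatment?** Yes for both, by Sections 4.1, 6.1.1 and 7.1 as set out above.

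**The plan's own figures.** There is none for birth weight to reproduce. Table 4 supplies the range of trial sizes, and it does reproduce. With one-sided alpha 0.000625, power 90%, relative risk 0.80, SP proportion p and q = 0.8p, the fixed-design total is

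2 × [(1−p)/p + (1−q)/q] × (z₁₋α + z₀.₉₀)² / (ln 0.80)².

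Multiplied by a group sequential inflation factor of 1.0235 (gamma(−4) efficacy, gamma(−6) non-binding futility, looks at 50, 70 and 100%), this gives 5044, 4205, 3552, 3029 and 2602 for p = 0.28, 0.32, 0.36, 0.40 and 0.44. The stated totals are 5044, 4206, 3552, 3030 and 2602. The 0.44 is inferred for the open top class.

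**Gain from adjustment.** Let R² be the share of variance explained by the added covariates beyond treatment and gravidity. Gravidity is already in the ANOVA, so a crude correlation between maternal weight and birth weight would not be the right input. Then

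- standard error ratio = √(1 − R²);
- equivalent gain in births = 1/(1 − R²) − 1;
- power at two-sided 0.05, single look, starting from 80% = Φ(2.802/√(1 − R²) − 1.960), and with 3.242 in place of 2.802 when starting from 90%.

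R² is not in the documents. Over an assumed range:

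| Assumed R² | Change in SE | Equivalent births | 80% power becomes | 90% power becomes |
|---|---|---|---|---|
| 0.01 | −0.5% | +1.0% | 80.4% | 90.3% |
| 0.05 | −2.5% | +5.3% | 82.0% | 91.4% |
| 0.10 | −5.1% | +11.1% | 84.0% | 92.7% |

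**In grams.** With an assumed birth-weight SD of 450 g, 1:1 allocation and no missing weights, the standard error of the difference is 450 × √(2/n), with n per arm:

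- total 2602: n = 1301, SE 17.6 g, 95% half-width 1.96 × 17.6 = 34.5 g;
- total 5044: n = 2522, SE 12.7 g, 95% half-width 1.96 × 12.7 = 24.9 g.

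At R² = 0.10 the half-width shrinks by 0.051 × 34.5 = 1.8 g or 0.051 × 24.9 = 1.3 g. At R² = 0.01 it shrinks by less than 0.2 g in both cases. An SD of 400-500 g moves the two standard errors to 15.7-19.6 g and 11.3-14.1 g. Fewer weighed live births would raise the standard errors but leave the percentage gains unchanged.

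**The case against.** The best case against raising this is that nothing is wrong. A stratum-adjusted ANOVA is a legitimate analysis of a randomized comparison, it matches the stratum-adjusted primary analysis, and one uniform rule for all continuous endpoints is easy to defend. Covariates for an other secondary endpoint are often settled in the SAP, and Section 9 says that the SAP may modify the protocol's plans. The gain rests on an R² that the protocol does not give, and at most it is a gram or two on the confidence half-width.

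Much of this stands. The size is assumed, it is small, and no decision in the protocol turns on it. The SAP argument does not remove the point: Section 9.2.2 does not leave the model open but lists its terms and the rule for choosing them. That the SAP may depart from the rule shows where a correction could be made, not that one was made.

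A reader might infer more than the documents support:

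- **That birth weight is analysed without adjustment, or with bias.** It is adjusted for gravidity, the factor the protocol itself links to higher risk. The estimate is unbiased and the type I error is kept.
- **That the trial's main conclusions are weakened.** The primary endpoint and low birth weight are analysed by a Mantel-Haenszel risk ratio. Early stopping uses only those two for efficacy and only the primary for futility. Continuous birth weight enters none of this and has no power claim that could fail.
- **That a material loss has been shown.** Without a standard deviation or correlation in the documents, only the direction is secure, and only if the covariates are prognostic.

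**Conclusion.** The point holds as a minor efficiency improvement, not as an error. By tying adjustment to a baseline value of the same variable, the protocol fixes a birth-weight model that omits pre-treatment maternal weight and gestational age already collected at Visit 1. On an assumed R² of 1-10% beyond treatment and gravidity, the standard error would fall by about 0.5-5%, worth about 1-11% more births on this endpoint. If the covariates proved uninformative, adjusting would cost essentially nothing at this sample size.

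**What to change.** In Section 9.2.2, or in the SAP before unblinded data are seen, make an exception for birth weight: an ANCOVA with treatment group, randomization strata, Visit 1 maternal weight and ultrasound gestational age at Visit 1. Replace a missing covariate by its mean across both arms, and keep the ANOVA as a supportive analysis.

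State explicitly that the covariate is gestational age at entry. Gestational age at delivery is observed after randomization and may itself be affected by treatment (premature birth is part of the primary endpoint), so adjusting for it could remove part of the effect being estimated.

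The cost is one sentence. It needs no new data, no change to the alpha for secondary endpoints, and no change to the sample size or interim rules. Fixing it in advance matters, because the same adjustment introduced after results are known would look data-driven.

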### 9.3. Outcome Research Analysis

Health economic outcomes will be assessed in terms of the health care resource utilization consumed by newborns/infants and mothers due to low birth weight, anemia, sexually transmitted diseases or sub-optimal pregnancy outcome. Measures of resource utilization will include in-hospital and out-of-hospital services for newborn/infant and mother, and associated care.

In-hospital services will include number of times of hospitalization, length of hospital stay and the numbers and durations of related admissions/re-admissions. Out-of-hospital services will include local health clinic/physician's office/outpatient hospital clinic including emergency room (without having to be admitted) to attend to a health complication(s). Data will be summarized descriptively by treatment group.

Analysis of health economics outcomes will include an analysis of the number of hospitalization times and durations of hospital stays as well as number of outpatient hospital visits. Statistical methods will include the Wilcoxon or t-test for durations of total hospital stays and number of outpatient hospital visits. Descriptive statistics will be used in summarizing the results of the individual items in the healthcare resource utilization questionnaire. Cost analysis of these items may be performed separately, outside the scope of the current analysis plan.

Contributing to the health economic impact endpoint is the physician/subject questionnaire.

#### 9.4. Safety Analysis

Adverse events, concomitant medications, laboratory safety tests including hemoglobin and urine test for glucose and protein, physical examinations, and vitals signs will be collected for each subject during the study according to the schedule of assessments. Standard safety reporting tables will summarize and list the safety data.

Each adverse event will be counted once according to the date of onset. If the adverse event onset was prior to the first dose of study drug and the event does not increase in severity after initiation of study drug, the adverse event is then considered to be a pre-treatment adverse event and will not be counted in the treatment-emergent adverse event incidence tables. If the onset is prior to the first dose of study drug and the severity increases thereafter, the event is counted as a treatment-emergent adverse event. An adverse event with onset after the first dose of study drug will be counted as a treatment-emergent adverse event. This rule is consistent with the treatment-emergent signs and symptoms (TESS) convention for counting adverse events.

#### 9.5. Interim Analysis

The study will employ a group sequential design with three unblinded analyses conducted at 50%, 70% and 100% of information time (percentage of subjects with data for the primary endpoint). Group sequential stopping rules will be used to stop the trial early for efficacy and futility (futility is non binding) at each of the 2 sequential analyses.

The overall alpha level will be 1-sided 0.000625 and the power will be approximately 90% (See Section 9.1) for establishing superiority of AZCQ over SP in proportion of subjects with sub-optimal pregnancy outcome (primary endpoint). Secondary efficacy endpoints will use an overall alpha level of 1-sided 0.025. The study was designed using the EAST software Version 5.1.

To protect the Type I error rate, the gamma (-4) function will be used for alpha spending for all efficacy endpoints. Similarly, the gamma (-6) function will be used for beta spending for the primary endpoint only. Early stopping for efficacy will only occur if both the proportion of subjects with sub-optimal pregnancy outcome (primary endpoint) and the proportion of subjects with LBW (key secondary) is statistically significantly lower in the AZCQ group compared to SP, as evaluated by the relative risk (primary analysis). Early stopping for futility will only be based on the primary endpoint.

The EAST software will be used to monitor the sequential analyses. It is important to note that the critical values for the stopping boundaries will depend on the percentage of subjects actually in each sequential analysis (the actual observed percentage of information). The new critical values will be calculated within EAST subject to the pre-defined alpha and beta spending functions specified for the design, in order to maintain the appropriate overall power and significance level.

090177e1811dafca\Approved\Approved On: 22-Feb-2010 14:41

The sequential analyses will use unblinded treatment codes, and be prepared by a group within Pfizer but external to the study team. An Independent Data Monitoring Committee (IDMC) external to Pfizer will then be used to formally make decisions on stopping or continuing the study based on the interim results, the predefined stopping regions, and the interim monitoring output from EAST. The membership of the IDMC and its charter, as well as the procedures for performing the interim analyses will be finalized and documented prior to the first interim analysis.

## **9.6. Independent Data Monitoring Committee (IDMC)**

An IDMC external from Pfizer will review interim analyses data and oversee evaluation of emerging safety data on an ongoing basis. The full composition of the IDMC and the guidelines for oversight of this study will be specified in the IDMC charter.

A sponsor statistical programmer external to the study team will prepare results necessary for the IDMC review and provide the results directly to the IDMC. The sponsor study personnel who are involved in the day to day operation of the trial will remain blinded to the results provided to the IDMC until the database lock for the final analysis.

